## Patient selection

### Inclusion criteria

Stage T1–2, N0, M0 (American Joint Committee on Cancer (AJCC) Staging, 8th Edition – i.e. tumor size ≤5 cm) prior to registration.Not a candidate for surgical resection, determined by any of the following:
Consultation with a thoracic surgeonDiscussion at multidisciplinary tumour conference with a surgeon presentPatient refusal of surgeryPathologically (histologically or cytologically) proven diagnosis of non-small cell lung cancer (NSCLC) is not required, but strongly recommended.
If the risk of biopsy is unacceptable, pathologic confirmation is not required providing there is growth over time on CT imaging and/or fluorodeoxyglucose (FDG) avidity that is strongly suggestive of a primary NSCLC.Eastern Cooperative Oncology Group (ECOG) performance status 0–3.Age ≥ 18.Life expectancy > 6 months.Fibrotic interstitial lung disease of any subtype, as diagnosed by a respirologist/pulmonologist and confirmed by central review.

### Exclusion criteria

Prior invasive malignancy except non-melanomatous skin cancer, unless the patient has been disease free for at least of 2 year.Prior thoracic radiotherapyPlans for the patient to receive other local therapy while on this study, except at disease progression;Plans for the patient to receive systemic therapy (standard chemotherapy, biologic targeted agents or immunotherapy) while on this study, except at disease progression. Patients are allowed to receive anti-fibrotic agents used in the treatment of IPF or non-IPF fibrotic ILD (e.g. nintedanib, pirfenidone), or steroids, if those are part of their current ILD treatment regimen. Other immunosuppressive drugs such as mycophenolate, azathioprine, cyclophosphamide, and rituximab must be stopped for 2 weeks prior and 2 weeks after treatment.Active pregnancyConcurrent administration of any drugs with known radiosensitive effects (e.g. Methotrexate).

## Pre-treatment evaluation

History/physical examination within 4 weeks prior to registration, including documentation of current medications and home oxygen use.HRCT scan of the thorax (with contrast unless medically contraindicated) within 12 weeks of registration. Slice thickness must be 1.5 mm or less with continuous (i.e. non-gapped) images. Each centre must communicate with their radiologists to ensure that CT scans are done using protocols adequate for ILD. The primary tumor dimensions will be measured on CT.Positron emission tomography (PET) scan of the entire body within 8 weeks of registration, using FDG.Pre-bronchodilator spirometry, lung volumes and diffusion capacity within 8 weeks prior to treatment.Assessment by a respirologist/pulmonologist within 4 weeks of enrollment, for the following purposes:
To optimize pulmonary function and treatment of ILD, if possible.To document subtype of ILD, and whether possible, probable or definite IPF exists.To document key clinical features related to ILD (per a questionnaire), required for central review.Mediastinal lymph node sampling by any technique is **allowed** but **not required**. Hilar or mediastinal lymph nodes ≤1 cm in short-axis diameter with no pathological PET uptake will be considered N0. Patients with hilar or mediastinal lymph nodes > 1 cm in short-axis diameter on CT or lymph nodes with abnormal PET uptake may still be eligible if biopsies of suspicious lymph nodes are negative for malignancy.Assessment for brain metastases is not mandated unless suspicious symptoms are present, in which case a contrast-enhanced magnetic-resonance imaging (MRI) of the brain is required. If MRI is contra-indicated due to claustrophobia or metal implants (or other reason), then CT is allowed.

### Central review

A central review of the standardized clinical data, HRCT, and any previous lung biopsies (if available) will be done to confirm subtype of ILD. The central review team will include a pathologist, respirologist, and radiologist.

The following information will be required for central review:
Clinical/Laboratory Data: Including clinical history, symptoms with date of onset, smoking history (including pack years and quit date), exposures, CTD features, serology (normal and abnormal), pulmonary function tests, and the subtype of ILD as determined by the treating respirologist.Pathology: slides (to be returned) and pathology reportsRadiology: Digital Imaging and Communications in Medicine (DICOM) images of thoracic CT scans (through Quantitative Imaging for Personalized Cancer Medicine (QIPCM)) and radiology reports

Patients will be assigned to a category of fibrotic ILD (i.e. IPF, idiopathic non-specific interstitial pneumonia, CTD-ILD, hypersensitivity pneumonitis, Unclassifiable ILD/other) and an ILD-GAP score will be assigned.

## Radiation therapy

### Concurrent medications

During radiation, patients are allowed to receive anti-fibrotic agents (e.g. nintedanib) or steroids, if those are part of their current ILD treatment regimen. Other immunosuppressive drugs such as mycophenolate, azathioprine, cyclophosphamide, and rituximab must be stopped for 2 weeks prior and 2 weeks after treatment.

### Dose/fractionation

The total dose will be 50 Gy in 5 fractions, given every second day. In the event that the dose is de-escalated to 50 Gy in 10 fractions or 45 Gy in 15 fractions, then the same prescribing principles apply (i.e. using a SABR-like technique) but these latter two fractionations are given daily.

### Immobilization

A stable and consistent immobilization technique is advised for all patients and all fractions to maximize inter-fraction reproducibility. Patients should be comfortably immobilized during treatment to minimize unnecessary motion due to discomfort and maximize intra-fraction reproducibility. Different immobilization systems may be utilized including a thermoplastic shell, alpha-cradle, Vac-Lok bag or none, per institutional standard. The immobilization setup should be identical to that used at simulation time.

### Imaging

Patients will undergo planning CT simulation with a 4-dimensional (4D)-CT, unless being treated with a system that accounts for motion without 4D-CT (e.g. CyberKnife). The use of IV contrast is not required. Axial CT images will be obtained throughout the region of interest**.** At each center, the local physicist or CT-simulation therapists will review the 4D-CT images and will perform the following quality assurance procedures: ensuring all end inspiration (0%) tags exist and are in the right place; ensuring that the quality of the 4D-CT images are acceptable (determined by Physics or CT-simulation therapists if standard at that institution); and that motion measurements in all 3 directions are performed.

### Motion management

Motion assessment is mandatory. The specific target motion of each patient must be quantified to determine if additional motion management strategies are required. If the tumor excursion is ≤1 cm, the internal target volume (ITV) approach is sufficient for treatment planning and dose-volume histogram (DVH) analysis, although standard institutional motion management strategies may be used as well. The design of the target volume should cover the primary lung cancer during breathing. If the tumor excursion is > 1 cm, acceptable motion management techniques for reducing target motion ≤1 cm include abdominal compression, active breathing control, active breath hold, free-breathing gating, gated breath hold or robotic tumor tracking (direct soft tissue or fiducial tracking).

### Volume definitions

The target lesion will be outlined by an appropriately trained physician and designated the gross tumor volume (GTV) on both the inspiratory and expiratory CT images. The target will generally be drawn using CT pulmonary windows; however, soft tissue windows should be used to avoid inclusion of adjacent vessels, atelectasis, mediastinal or chest wall structures within the GTV. This target will not be enlarged whatsoever (i.e. no “margin” for presumed microscopic extension); rather, it will only include areas consistent with gross tumor (i.e., the GTV and the Clinical Target Volume, CTV, are identical). PET images may be used at the discretion of the treating oncologist, but consistent with International Atomic Energy Agency (IAEA) guidelines, CT should be used to determine the boundary between tumor and normal tissue, as PET images are subject to thresholding effects.

An ITV is generated from the outlined GTV on the inspiratory and expiratory CT datasets. An additional 0.5 cm will be added in all planes to constitute the planning treatment volume (PTV). Depending on institutional practice, the Exhale phase may be used as a primary dataset for treatment planning with fusion of the inhale, maximum intensity projection (MIP) and average. Alternatively, the Average phase may also be used as the primary dataset. The GTVs contoured on these datasets will define the internal GTV (IGTV). This contour may be used to define the PTV using standard margins or for image registration with cone beam CT (CBCT).

For respiratory gating treatment, if used, planning will be performed on a subset average CT dataset (usually labeled either 30–60% Avg CT or 40–70% Avg CT) generated by Physics. This is an average CT over the intended gated interval. Therefore, the GTV that is delineated on this scan will incorporate residual motion in the intended gated interval. The 0% phase will also be fused to this dataset. The PTV for planning will include the GTV delineated on the subset average CT and setup uncertainty. The GTV_0% should also be delineated and combined with the GTV delineated on the subset average CT to define an additional volume labeled IGTV_CBCT. This contour may be used for image guidance with CBCT only.

### Dosimetry

Treatment can be delivered using static beams (either 3D-conformal radiotherapy or intensity-modulated) or rotational therapy (volumetric modulated arc therapy, or Tomotherapy). Only photon (X-ray) beams of 10 MV or less produced by linear accelerators will be used.

For purposes of dose planning and calculation of monitor units for actual treatment, this protocol will require tissue density heterogeneity correction. Successful treatment planning will require accomplishment of all of the following criteria:
Prescription isodose surface: The prescription isodose surface will conformally cover 95% of the target volume (PTV), such that 99% of the PTV will also receive at least 90% of the prescription dose. (PTV D95% = 100% of prescription dose and D99% = 90% of prescription dose)Target dose heterogeneity: The dose at the prescription isodose surface must be between 60 and 90% (inclusive) of the dose at the normalization point of the plan. The prescription isodose surface is typically 80% of the dose at the normalization point, though the allowed range enables flexibility to optimize dose to organs at risk (OARs), especially the lung.High dose spillage (as per the RTOG 0813 [16] protocol):
Location: Areas with dose > 105% of the prescription dose should be located primarily within the PTV itself. The cumulative volume outside the PTV volume with dose > 105% of prescription dose should be no more than 15% of the PTV volume.Volume: Conformality of PTV coverage will be determined by the R100 (the ratio of the volume of the prescription isodose to the volume of the PTV), R50 (The ratio of the volume of 50% of the prescription dose isodose to the volume of the PTV), and D2cm (the maximum total dose over all fractions in Gray (Gy) to any point 2 cm or greater away from the PTV in any direction), as per Table 3.All critical organ dose-volume constraints in Table 2 must be respected. **Lung dose constraints may not be exceeded for any reason.**

**Table 2 Tab2:** Recommended dose constraints for non-lung organs. 5-fraction and 8-fraction constraints based on RTOG 0813 protocol [16], SABR-COMET protocol [17], and Timmerman et al [18]. Constraints for other fractionation schemes are derived using BED_3_

Structure		Number of Fractions		
		5	10	15
Spinal Cord (contoured as spinal canal)	Max	30 Gy	34.5 Gy	39.5 Gy
	< 0.25 cc	22.5 Gy	29 Gy	33 Gy
	< 1.2 cc	13.5 Gy	17 Gy	19 Gy
Esophagus	Max	35 Gy	43.5 Gy	50.5 Gy
	< 5 cc	27.5 Gy	35.5 Gy	41 Gy
Ipsilateral Brachial Plexus	Max	32 Gy	42.5 Gy	49 Gy
	< 3 cc	30 Gy	39.5 Gy	45.5 Gy
Heart	Max	38 Gy	50 Gy	58.5 Gy
	15 cc	32 Gy	42.5 Gy	49 Gy
Great Vessels	Max	53 Gy	71.5 Gy^a^	84 Gy^a^
	10 cc	47 Gy	63.5 Gy	74.5 Gy^a^
Trachea and Ipsilateral Bronchus	Max	38 Gy	43.5 Gy	50.5 Gy
	4 cc	18 Gy	23 Gy	26 Gy
Skin	Max	32 Gy	42.5 Gy	49 Gy
	10 cc	30 Gy	39.5 Gy	45.5 Gy
Stomach	Max	32 Gy	43.5 Gy	50.5 Gy
	10 cc	28 Gy	37 Gy	42.5 Gy
Liver	At least 700 cc	< 21 Gy	< 23.5 Gy	< 26.5 Gy
Chest Wall	Keep as low as reasonably achievable, do not compromise PTV, respect PTV conformality parameters			

^a^Although calculated tolerance dose is much higher, seek to limit any point of the organ to 110% of prescription dose. Non-adjacent wall must always be limited to 105% (see below)

### Critical structures

Dose-volume histograms must be generated for each critical structure so that the dose-volume constraints can be evaluated. Instructions for contouring the critical structures are provided below and reflect common radiotherapy contouring procedures, as per RTOG 0813 [16]:
Spinal cord: the spinal cord is contoured based on the bony limits of the spinal canal. The spinal cord should be contoured on every slice starting at least 10 cm superior to the most superior extent PTV to at least 10 cm inferior to the most inferior extent of the PTV.Esophagus: the esophagus will be contoured using the mediastinal window on CT corresponding to the mucosal, submucosa, and all muscular layers of the esophagus. The esophagus should be contoured on every slice starting at least 10 cm superior to the most superior extent of the PTV to at least 10 cm inferior to the most inferior extent of the PTV.Ipsilateral brachial plexus: the ipsilateral brachial plexus originates from the spinal nerves exiting the neuroforamina from C5 to T1. The detailed contouring procedures can be found in the RTOG contouring atlas [19].Heart: the heart and the pericardial sac will be contoured together as the heart critical structure. The superior aspect (or base) of the heart will begin at the level of the inferior aspect of the aortic arch and extend inferiorly to the apex of the heart.Trachea and proximal bronchial tree: the trachea and proximal bronchial tree will be contoured as two separate structures using mediastinal windows on CT to correspond to the mucosal, submucosa and cartilage rings and airway channels associated with these structures. For this purpose, the trachea will be divided into two sections: the proximal trachea and the distal 2 cm of trachea. The proximal trachea will be contoured as one structure, and the distal 2 cm of trachea will be included in the structure identified as proximal bronchial tree.
Contouring of the proximal trachea should begin at least 10 cm superior to the extent of the PTV or 5 cm superior to the carina (whichever is more superior) and continue inferiorly to the superior aspect of the proximal bronchial tree.The proximal bronchial tree will include the most inferior 2 cm of distal trachea and the proximal airways on both sides. The following airways will be included according to standard anatomic relationships: the distal 2 cm of trachea, the carina, the right and left mainstem bronchi, the right and left upper lobe bronchi, the intermedius bronchus, the right middle lobe bronchus, the lingular bronchus, and the right and left lower lobe bronchi. Contouring of the lobar bronchi will end immediately at the site of a segmental bifurcation. If there are parts of the proximal bronchial tree that are within GTV, they should be contoured separately, as “proximal bronchial tree GTV”, not as part of the “proximal bronchial tree”.Whole lung: both the right and left lungs should be contoured as one structure. Contouring should be carried out using pulmonary windows. All inflated and collapsed lung should be contoured.PTV plus 2 cm: A quality-assurance structure 2 cm larger in all directions from the PTV is required to determine the maximum dose at any point 2 cm from the PTV. Most treatment planning systems have automatic contouring features that will generate this structure.Great vessels: the great vessels (aorta, venae cavae, pulmonary artery and pulmonary vein) will be contoured as a single structure using mediastinal windows to correspond to the vascular wall and all muscular layers of these great vessels. The great vessels should be contoured on every slice starting at least 5 cm superior to the most superior extent of the PTV to at least 5 cm inferior to the most inferior extent of the PTV. The distal extent of the right and left pulmonary arteries will be the bifurcation to the basal segmental arteries. The pulmonary veins will be contoured until the superior and inferior pulmonary veins bifurcate to the segmental and basal veins.Chest wall: the chest wall includes the ribs and intercostal muscles and nerves. It should be defined as a 2 cm anterior, lateral, and posterior, expansion of the lung, not including the lung itself, the mediastinum, diaphragm, GI structures, or the spinal cord.

### Dose constraints for organs besides lung parenchyma

Table 2 lists maximum dose limits to a point or volume for several critical organs, depending on the number of fractions. Note that the number of fractions will be 5 unless the dose is de-escalated due to safety reasons. These dose constraints have been calculated using the BED formula and are generally considered iso-toxic, meaning that they are considered to portend an equal risk of toxicity to those organs, across the different fractionation schemes. This is in distinction to the lung dose constraints below, which are NOT iso-toxic, meaning that the risk of toxicity increases with higher dose levels.

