Alternatively, it may be necessary to reduce the dose of SABR, at the risk of compromising tumor control. Adjustments to the SABR fractionation schedule may reduce the risk of toxicity, while still maintaining some benefit. Radiation dose is expressed in Gray (Gy), with most SABR treatments delivering approximately a total dose 50–60 Gy. This total dose is divided up into smaller individual fractions of radiation. Conventional radiotherapy employs fraction sizes of approximately 2 Gy per day, 5 days per week, and would require 30 fractions to deliver 60 Gy. This prolonged treatment time (i.e. 6 weeks of treatment) may allow for tumor repopulation, compromising treatment outcomes. With SABR, common fractionations include 54 Gy in 3 fractions (i.e. 18 Gy per fraction), 48 Gy in 4 fractions (i.e. 12 Gy per fraction) and 60 Gy in 8 fractions (i.e. 7.5 Gy per day). SABR fractions are often given every second day (or even more widely spaced) to maximize the time for normal tissue repair between fractions.

To compare the potency of these different radiation dose fractionations, a formula called the biologically effective dose (BED) is used. BED takes into account the total number of fractions, the dose per fraction, and the intrinsic radiation response curve of the individual tissues treated. BED is calculated according to the formula $$ {BED}_{\alpha /\beta }= nd\left(1+\frac{d}{\alpha /\beta}\right) $$, where *α*/*β* is the alpha/beta ratio of the tissue (assumed to be 10 Gy for NSCLC and 3 Gy for normal lung tissue), *n* is the total number of fractions of radiation therapy and *d* is the dose per fraction.

The BED_10_ is used to predict the response of tumor, and also of acutely-responding normal tissues (e.g. skin and mucosa). A higher BED_10_ is associated with a higher chance of local control, and a value of BED_10_ ≥ 100 is considered a minimum threshold for SABR [14]. The BED_3_ is used to predict the response of normal lung parenchyma (i.e. the risk of radiation pneumonitis). A lower BED_3_ is expected to be associated with a reduced risk of pneumonitis. However, efforts to reduce the BED_3_ will also lead to reductions in BED_10_, compromising the effectiveness of SABR. (For specific BED_10_ and BED_3_ values used in the studies included in the meta-analysis, see Additional file 1).

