#### Note on central tumors

When the GTV tumor is within 2 cm of a central structure (e.g. heart, trachea), it will be considered a central tumor. In such a scenario, the dose constraints to central structures in Table 2 are often not achievable. These should be planned using the same approach as in the RTOG 0813 study, which determined the safe dose level of central tumors for a 5-fraction SABR regimen. In such an approach, the PTV coverage is not compromised, but the OAR dose is to be kept as low as possible. This applies to the esophagus, heart, great vessels, trachea, and ipsilateral bronchus. For the esophagus, great vessels, trachea, and ipsilateral bronchi, the non-adjacent wall of the structure limited to a maximum dose of 105% of prescription dose. In contrast, maximum doses from the above table for the spinal cord, brachial plexus, skin, and stomach are NOT to be exceeded.

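### Five of the 18 organ limits in Table 2 are not BED3-equivalent between 5 and 10 or 15 fractions, although the text calls the table iso-toxic; of these five, only the stomach maximum is looser

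*Protocol article*

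**What the plan says.** Table 2 (Dosimetry) prints non-lung organ limits for 5, 10 and 15 fractions. Its caption makes two statements about their origin: "5-fraction and 8-fraction constraints based on RTOG 0813 protocol" and two further published sources, and then "Constraints for other fractionation schemes are derived using BED_3". No 8-fraction column is printed.

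The section on dose constraints for organs besides lung parenchyma describes the result: "These dose constraints have been calculated using the BED formula and are generally considered iso-toxic". It explains this as an "equal risk of toxicity to those organs, across the different fractionation schemes", and contrasts it with the lung limits, which it says are not iso-toxic.

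The formula is in the Rationale for a study: BED = nd(1 + d/(alpha/beta)), with alpha/beta "assumed to be 10 Gy for NSCLC and 3 Gy for normal lung tissue". The caption carries the value 3 over to the other organs.

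On how binding the limits are, the Dosimetry section requires all Table 2 constraints to be respected. The note on central tumors relaxes the approach for some structures but adds that "maximum doses from the above table for the spinal cord, brachial plexus, skin, and stomach are NOT to be exceeded". The quality assurance section allows organ limits to be exceeded with the principal investigator's approval.

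**The concern.** If the 10- and 15-fraction limits carry the same risk as the 5-fraction limits under BED3, each row should give about the same BED3 in all three columns. The printed values suggest otherwise before any calculation. Esophagus, trachea and stomach share 43.5 and 50.5 Gy at 10 and 15 fractions, although their 5-fraction maxima are 35, 38 and 32 Gy.

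The 10- and 15-fraction columns are used for patients in a cohort or ILD subtype whose dose has been lowered after treatment-related deaths. They are also used for patients whose lung constraints cannot be met at 5 fractions. A planner who relies on the equal-risk statement would be misinformed about relative organ risk for exactly these patients. Two of the rows in question, cord and stomach maxima, are among those that the central-tumor note says may not be exceeded.

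**Working it through.** **Formula.** With total dose D in n fractions and alpha/beta 3, BED3 = D(1 + D/(3n)).

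**Check on the protocol's own figures.** The regimen values in the Abstract and Discussion reproduce:
- 50 Gy in 5: 50(1 + 10/10) = 100 and 50(1 + 10/3) = 217
- 50 Gy in 10: 50(1 + 5/10) = 75 and 50(1 + 5/3) = 133
- 45 Gy in 15: 45(1 + 3/10) = 58.5 and 45(1 + 3/3) = 90

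**The five discrepant rows.** Printed limits are from Table 2.

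| Row | Printed Gy, 5/10/15 | BED3, 5/10/15 | Change in BED3 from 5 fractions, at 10 / 15 |
|---|---|---|---|
| Spinal cord max | 30 / 34.5 / 39.5 | 90.0 / 74.2 / 74.2 | -17.6% / -17.6% |
| Esophagus max | 35 / 43.5 / 50.5 | 116.7 / 106.6 / 107.2 | -8.7% / -8.1% |
| Trachea and bronchus max | 38 / 43.5 / 50.5 | 134.3 / 106.6 / 107.2 | -20.6% / -20.2% |
| Liver (at least 700 cc below) | 21 / 23.5 / 26.5 | 50.4 / 41.9 / 42.1 | -16.8% / -16.5% |
| Stomach max | 32 / 43.5 / 50.5 | 100.3 / 106.6 / 107.2 | +6.3% / +6.9% |

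Worked example, stomach maximum: 32(1 + 32/15) = 100.3; 43.5(1 + 43.5/30) = 106.6; 50.5(1 + 50.5/45) = 107.2.

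**The other 13 rows.** To compare in Gy, the 5-fraction BED3 is carried to n fractions by D = [-3n + sqrt((3n)^2 + 12n x BED3)]/2. These 13 rows then differ from the printed limit by at most 0.83 Gy. That is close, but it is not rounding alone. The table is rounded to 0.5 Gy, so rounding explains about 0.25 Gy, and 11 of the 13 rows exceed that in at least one column, always on the looser side. The five rows above differ by 1.6 to 7.9 Gy, so there is a clear break between the two groups.

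**Internal consistency.** A single conversion must send equal 5-fraction limits to equal limits at 10 and 15. Table 2 does not:
- 32 Gy goes to 42.5 / 49 for skin, but to 43.5 / 50.5 for stomach.
- 38 Gy goes to 50 / 58.5 for heart, but to 43.5 / 50.5 for trachea.
- 30 Gy goes to 39.5 / 45.5 for skin (10 cc), but to 34.5 / 39.5 for cord maximum.

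This does not depend on which single alpha/beta is used. At alpha/beta 2 the cord, esophagus, trachea and liver gaps widen, while the stomach gap narrows to +0.7 / +0.25 Gy. At 10 most of the other rows fail. Organ-specific values could produce such a pattern, but the caption specifies BED3.

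**The case against.** The strongest reply is that the derivation itself may be correct. The caption does not say that the 10- and 15-fraction limits come from the 5-fraction column; it names 8-fraction sources as well. In the disputed rows the 10- and 15-fraction columns agree with each other in BED3, and they convert back to near-round 8-fraction values: about 32 Gy for cord, 40 Gy for esophagus, trachea and stomach, and 22 Gy for liver. One shared 8-fraction value of 40 Gy would explain the repeated 43.5 and 50.5 Gy. This is plausible, though it is inference, because no 8-fraction column is shown. It means that a calculation slip has not been demonstrated. It does not rescue the claim of equal risk across the printed schemes, which include 5 fractions, and the hedge that the limits are generally considered iso-toxic does not cover BED3 gaps of 6 to 21%.

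A reader might infer that the stricter rows cost target coverage. The documents do not support that. Every printed limit at 10 and 15 fractions is higher than at 5 fractions, both in Gy and as a share of prescription. For example, the cord maximum is 30/50 = 60%, 34.5/50 = 69% and 39.5/45 = 88%. For central tumors the protocol also states that target coverage is not compromised for esophagus, trachea and bronchus.

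It is also fair that the stomach gap is modest, that its not-to-be-exceeded status is stated in the note on central tumors, and that Table 2 is titled as recommended constraints.

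**Conclusion.** The equal-risk statement is not true of Table 2 as printed. Five of 18 rows are not BED3-equivalent between the 5-fraction column and the other two: four are biologically stricter at 10 and 15 fractions (by about 8 to 21% in BED3), and the stomach maximum is looser by 6 to 7%. The other 13 rows agree within about 0.9 Gy.

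This rests on the protocol's own formula and on the alpha/beta of 3 that the caption names. It says nothing about which printed limit is clinically right. Nor should it be read as showing that the lower-dose schedules are less safe overall: among the five discrepant rows only the stomach maximum loosens, and the loosening elsewhere stays under 0.9 Gy.

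The point is minor for the trial's statistics. The primary analysis is confined to patients treated with 50 Gy in 5 fractions, so sample size, power and the decision on survival do not change. It deserves correction because the affected columns serve patients moved to another schedule for safety or because of lung constraints.

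**What to change.** Reconcile three places: the Table 2 caption, the five discrepant rows, and the iso-toxic statement in the section on organs besides lung parenchyma. Check the stomach and spinal cord maxima first, since the protocol treats both as limits not to be exceeded and they depart in opposite directions. For every limit not converted from the 5-fraction column, state its source; if an unprinted 8-fraction set was the starting point, say so. Limit the iso-toxic statement to the rows where it holds. The responsible physics and clinical team must settle the limits themselves; none is proposed here. The cost is one table check by physics and a wording change, with no effect on the design or analysis.
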